#### Assessment of activities of daily living

To assess the independence of individuals to perform activities of daily living will be used the Lawton and Brody Scale [41], reliable and validated measure for the elderly population. The evaluation is performed through a questionnaire containing questions, whose answers can be categorized as independent (3 points), partially dependent (2 points) or dependent (1 point). If the participants reach the maximum score of 25 points, they will be considered completely independent; 5 to 21 points indicates partial dependence and less than 5 points indicates complete dependence.

#### Assessment of quality of life

We will use the WHO Quality of Life Instrument to assess quality of life [35], which will be administered as an interview.

This instrument consists of 26 items divided into four domains: physical, psychological, social relations and environment. Each item will be rated with a score (from 1 to 5) awarded according to the domain being evaluated: very bad, dissatisfied, nothing or never (1 point); too little, bad, sometimes dissatisfied (2 points); medium, neither bad nor good, neither satisfied nor dissatisfied, more or less often (3 points); very, good, quite, good, satisfied and very often (4 points); completely, very good, very satisfied, extremely, completely, very good and always (5 points).

The score ranges from 26 to 130 points, with higher scores indicating a better quality of life.

##### Evaluation of muscle strength

To assess the strength of the lower limbs, consideration will be given to the quadriceps muscle. The test used will be the Medical Research Council evaluation of muscle strength [36] which is tested manually. The interpretation of the result is as follows: if the subject shows no contraction, the degree of force is zero; grade 1 strength is when there is draft muscle contraction; grade 2 strength is when the individual performs muscle contraction and pro-gravity movement (severity eliminated); grade 3 strength is when the individual can perform muscle contraction (movement) against the force of gravity; grade 4 strength is when the individual can perform slight contraction with the force of gravity; grade 5 strength is when the individual can perform contraction with movement against gravity and moderate resistance.

##### Data analysis

To identify data normality and cases of non-normal distribution, data distribution analyses will be performed by visual analysis of the histograms of each treatment group. Descriptive statistics will be used as measures of central tendency and dispersion, mean and standard deviation will be used for quantitative variables, frequency will be used for categorical variables and the median and the interquartile range will be used for nonparametric variables.

An ANOVA of two factors followed by the Bonferroni test will be used for comparative analysis between groups (active and sham tDCS) along the time points (pre- and post-training).

A *P* value <0.05 will be considered indicative of statistical significance, and Pearson correlation will be used to calculate the relationship between Glittre-ADL performance and the secondary outcomes of the capacity to walk (6MWT), balance (mini-BESTest), FIM, instrumental activities of daily living, quality of life, and evaluation of muscle strength at pretraining, following treatment and at 30-day follow-up.

Individual results will be analyzed later for each outcome. These individual data will be an important complement to identifying the clinical relevance of the results [42].

Clinical characteristics, especially outcome-related characteristics, and functional capacity (Glittre-ADL test) will be compared at baseline to ensure homogeneity of the groups. The significance level of *P* < 0.05 refers to the alpha risk adopted in the ANOVA test. If there is a significant difference between groups, times, or interactions between groups and time, the *P* value of the multiple comparison analysis from the Bonferroni post-hoc test will be adopted.

All analyses will be processed using the SPSS program (IBM SPSS Statistics for Windows, Version 22.0, released in 2013, IBM Corp., Armonk, NY, USA). In case of dropouts and missing data, an intention-to-treat analysis will be performed using the appropriate imputation method according to the missing standard, the data will be analyzed when participants receive no treatment (or are under a control condition) depending on the group assigned, and when outcome measures are available an analysis will be performed as if the individuals had received the treatment (or a control condition).

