**Discussion:**

We hypothesize that tDCS, when associated with multicomponent training, can potentiate and prolong the effects of this training on the functional capacity of the elderly. If this hypothesis is confirmed, this protocol may contribute to a longer-lasting physical rehabilitation of the elderly, encouraging them to maintain their independent daily activities for longer.

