tDCS is a neuromodulatory technique that induces excitability of the cerebral cortex without inducing action potential and can modify the resting potential of the neuronal membrane, consequently modulating the neuronal firing rate [23]. It consists of the application of a lowintensity electric current in specific regions properly measured under the scalp using two electrodes that act on the balance of ions inside and outside the neural membrane, stimulating changes in the resting threshold [23]. Anodic current increases cortical excitability, favoring membrane depolarization, and cathodic current decreases cortical excitability, favoring membrane hyperpolarization [20, 21].

Based on this information, this study hypothesizes that tDCS is capable of enhancing and prolonging the effects of multicomponent training on the functional capacity of the elderly, making this type of physical training more effective.

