### Objectives

The main objective of this study will be to evaluate the functional capacity of the elderly participants before and after participation in physical activity with multicomponent training associated with active or sham tDCS and to verify if these results are maintained 30 days after the end of the training.

Secondary outcomes will correlate the performance of the primary outcome (functional capacity) with the walking capacity, balance, muscle strength and functional independence after multicomponent training alone or when associated with tDCS.

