### Allocation and blindness

The NeuroConn DC-STIMULATOR PLUS device has settings that allow one to select the active or sham protocol by codes consisting of a five-digit numeric sequence (provided by the manufacturer). There are 200 different possibilities (100 for each stimulus type of active or sham), so each participant will have their own code. Access to these numbers will only be provided for one of the researchers (researcher 1). This researcher will randomize the participants (http://www.randomization.com) and enter the codes according to the randomization (active group or sham) into the equipment, and thus it is not possible for the researcher who will apply the treatment and evaluate the results (researcher 2) to know the code and what is the treatment, ensuring blinding.

To ensure blinding of the participants and researcher 2 (a double-blind study) during stimulation, the device will appear switched on for both protocols (with no different external visual cues); however, for the active protocol the device will be programmed to operate for 20 min. For the sham protocol, the device will emit current for 20 s and then reduce this to zero (this programming is done by the manufacturer).

Researcher 2 will explain to the participant that they may feel a slight tingling that may continue or subside over time.

When treatment is over, researcher 1 will give researcher 2 a table for data analysis, with the names of participants divided into groups 1 and 2 (according to randomization), without treatment identification.

Researcher 2 will only know which group has received active and which group has received sham tDCS when the 30-day follow-up statistical analyses are complete.

To check blinding to treatment, a questionnaire will be delivered to each participant and researcher 2 at the end of each session asking whether the treatment was applied as active or sham tDCS.

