#### Assessment of functional capacity

To assess functional capacity, the Glitter-ADL test [31] will be used at three points (pretraining, post-training and 30 days after the end of training). T's an instrument validated for patients with chronic obstructive pulmonary disease, with acceptable reliability (95% CI −0.20 to −0.54).

The Glittre-ADL test is an instrument validated for patients with chronic obstructive pulmonary disease, with acceptable reliability (95% CI −0.20 to −0.54) [31], which has been previously tested in healthy older adults [38, 39], showing excellent intra-rater (ICC 0.90, 95% CI 0.86–0.93) and inter-rater (ICC 0.91, 95% CI 0.88–0.94) reliability (*P* < 0.001 for both). The intra-rater standard measurement error was 0.03 min and the inter-rater standard measurement error was 0.05 min. The minimal detectable change for intra-rater was 0.40 min and for inter-rater was 0.07 min.

The Glittre-ADL test consists of getting up from a chair with a backpack containing one weight (2.5 kg for women and 5.0 kg for men), walking 5 m on a flat track, going up and down steps measuring 17 cm in height and 27 cm in depth, and walking another 5 m to a set of three shelves, one at the top (at shoulder level), one in the middle (at pelvic waist level) and one at floor level. When reaching the shelves, the participant should transfer three balls, weighing 1 kg each, from the top to the middle and then to the bottom shelf and finally from the bottom shelf to the floor, and then return the balls in the same sequence until they reach the upper shelf. The task should be repeated in the reverse sequence until the participant is sitting again.

The complete test consists of five repetitions of this circuit, which should be performed as quickly as possible. Performance is given by the running time (in minutes) of the five laps with a shorter the time indicating better performance, considering a clinically important improvement between 7 and 40 s [38]. To be considered as preserved functional capacity, the test must be performed in approximately 2 min [39].

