## Discussion

The present study will aim to compare the effects of multicomponent training associated with active and sham tDCS on the functional capacity in elderly participants after 24 training sessions and 30 days after the end of training.

This objective was based on research showing that the use of tDCS combined with other therapies has promising effects, as the sum of the two combined techniques can improve cortical activity and motor learning. Fujiyama et al. [43] observed improvements in upper limb motor skills in the elderly with isometric strength training when associated with the simultaneous use of tDCS compared with a control group.

The hypothesis for this study is that after tDCS application, neuronal membrane depolarization will occur, which will facilitate any subsequent therapeutic stimulus, as long-term potentiation is released after anodal tDCS. Therefore, this effect will facilitate motor learning and cognitive training over a long period [44, 45].

These results are important because older people lose their cognitive ability over time, thus justifying the decision to stimulate the area of the lateral dorsal prefrontal cortex which is responsible for the performance of executive functions and for the planning and precise control of complex movement sequences.

Metuki et al. [46] and Hecht et al. [47] report that, by stimulating this area, better actions regarding decisions, memory and movement precision of motor tasks can be observed.

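### The between-arm ANOVA names only the pre- and post-training visits, so the 30-day, 'prolong' part of the main hypothesis has no specified test

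*Protocol article*

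**What the plan says.** **The question.** The Objectives section adds to the main objective an aim "to verify if these results are maintained 30 days after the end of the training". The Introduction hypothesises that "tDCS is capable of enhancing and prolonging the effects of multicomponent training on the functional capacity of the elderly", and the abstract says that tDCS "can potentiate and prolong the effects of this training". The Discussion is the most explicit. It sets out to compare multicomponent training with "active and sham tDCS on the functional capacity in elderly participants after 24 training sessions and 30 days after the end of training".

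**The data.** The Glittre-ADL test, the primary outcome, is given at "three points (pretraining, post-training and 30 days after the end of training").

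**The analysis.** The Data analysis section names one test that compares the arms, a two-factor ANOVA followed by Bonferroni, and describes it as a "comparative analysis between groups (active and sham tDCS) along the time points (pre- and post-training"). In that section the 30-day visit is named only for the Pearson correlations of Glittre-ADL with "quality of life, and evaluation of muscle strength at pretraining, following treatment and at 30-day follow-up" and the other secondary measures.

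**The blinding text.** Researcher 2 learns the arm labels only "when the 30-day follow-up statistical analyses are complete". No method for those analyses is given.

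**The concern.** The hypothesis has two parts: a larger effect at the end of training, and an effect that lasts. The named ANOVA addresses the first part only. The correlations at 30 days relate one outcome to another and do not compare the arms. An analyst who follows the text literally would fit a two-by-two ANOVA and leave out a visit that every participant is due to attend.

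If the 30-day comparison is settled only later, several choices stay open until the data are in hand: the contrast, the reference visit, and whether the multiplicity correction covers it. Those choices can change the conclusion on prolongation in a trial of 28 people.

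**Working it through.** **1. Can post-training include the 30-day visit?** No. The section on assessment of functional capacity lists post-training and 30 days as separate points. The Data analysis section does the same for the correlations, where the visit following treatment and the 30-day follow-up are separate items. The ANOVA wording therefore covers two of three visits.

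**2. Does the sample size show which analysis was meant?** Inputs from Sample size calculation: means 172.05 s and 203.82 s, SD 30.79 s, alpha 0.05, power 80%, 22 participants, raised to 28 for 20% dropout, by a repeated-measures ANOVA F test.

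- Difference = 203.82 − 172.05 = 31.77 s; d = 31.77/30.79 = 1.032; f = d/2 = 0.516.
- Between-factors F test: λ = f²·N·m/(1 + (m − 1)ρ), with 1 and N − 2 degrees of freedom. The number of measurements m and the correlation ρ are not stated, so both are assumptions.

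| m | ρ | λ at N = 22 | Power at N = 22 | N for 80% |
|---|---|---|---|---|
| 3 | 0.5 | 8.78 | 0.805 | 22 |
| 2 | 0.5 | 7.81 | 0.757 | 26 |
| 2 | 0.3 | 9.01 | 0.815 | 22 |

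- Dropout: 22/(1 − 0.20) = 27.5, rounded up to 28.

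The stated 22 and 28 are reproduced with three visits and ρ = 0.5. Two visits with ρ of about 0.3 also give 22, so this hints at a three-visit design but does not prove it. This F test averages the arm difference over all visits, baseline included. Its power is therefore not the power for prolongation.

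**3. Power of one active-versus-sham contrast at 30 days.** Two-sample t test, noncentrality d·√(n/2), assuming that the pilot difference and SD hold at 30 days.

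- 14 per arm: 1.032 × √7 = 2.73, 26 df. Power is 0.748 at two-sided 0.05 and 0.639 at 0.025 (Bonferroni over two contrasts).
- 11 per arm: 1.032 × √5.5 = 2.42, 20 df. Power is 0.634 at 0.05 and 0.510 at 0.025.

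These are for raw times. For change from baseline the SD is 30.79 × √(2(1 − ρ)): 36.4 s at ρ = 0.3, 30.79 s at 0.5 and 23.8 s at 0.7. If the difference in change is also 31.77 s, unadjusted power with 14 per arm is 0.60, 0.75 and 0.92; with 11 per arm it is 0.50, 0.63 and 0.84.

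**4. Precision with 14 per arm.**

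- Between arms at 30 days, raw times: t(26) × SD × √(2/14) = 2.056 × 30.79 × 0.378 = 23.9 s.
- Within-arm change from post-training to 30 days: t(13) × 30.79 × √(2(1 − ρ))/√14, with t(13) = 2.160. This is 21.0 s at ρ = 0.3, 17.8 s at 0.5 and 13.8 s at 0.7.

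The functional capacity section takes an improvement of 7 to 40 s as clinically important. A within-arm change estimated at zero would still leave losses of roughly 14 to 21 s inside the interval.

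**The case against.** The strongest reply is that the 30-day comparison is unspecified, not excluded. Group-coded 30-day analyses are expected before unblinding, and the Discussion states the aim as a comparison of arms at 30 days. The Data analysis section also sends a significant difference between times to a Bonferroni multiple-comparison test, which a two-level time factor would not need. With the sample-size hint, this points to an unfinished parenthesis rather than a decision to drop the visit. A separate analysis plan may give the method.

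Most of that stands, and it limits the point. A reader might infer that the trial cannot support or refute prolongation at all. The documents do not show that: the data will exist and the intent to analyse them is plain. What does not stand is treating the matter as detail left to another document. The article does not stay silent on the time points. It states them, and leaves out one that its own objective requires.

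Two further inferences go too far. One is that the investigators will take a non-significant change from post-training to 30 days as maintenance; no section says so. The other is that such a result would be compatible with losing more than half of the 31.77 s planning difference. At a zero estimate this needs a half-width above 15.9 s, which fails once ρ exceeds about 0.6. It also sets a within-arm change against a between-arm difference.

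**Conclusion.** The ANOVA sentence is wrong as written. It conflicts with the main objective, the hypothesis and the Discussion, and the 'prolong' part of the hypothesis has no specified between-arm test. The textual conflict rests on no assumption.

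The figures describe what a corrected analysis can deliver. They rest on the pilot difference and SD holding at 30 days, and the figures for change rest on an assumed correlation. They show that the 30-day contrast of raw times falls short of the stated 80% power, and that precision is limited. They do not measure the harm done by the omission.

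**What to change.** - In the Data analysis section, give the time factor three levels: pre-training, post-training and 30-day follow-up.
- Name the active-versus-sham contrast in Glittre-ADL change from baseline to 30 days, within the group-by-time analysis, as the test of prolongation. Report it with a 95% CI and include it in the Bonferroni procedure already planned.
- Report the change from post-training to 30 days by arm with its 95% CI, and do not read non-significance alone as maintenance.
- Disclose the power of the 30-day contrast. The sample size was not shown to give 80% for it.

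The cost is a few sentences. No visit, measurement or participant is added, because the 30-day data are already scheduled. The change should be made and dated before the arm labels are released. The price is candour about power: including a further contrast under Bonferroni lowers it, for example from about 75% to 64% with 14 per arm for two contrasts of raw times.

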#### Sample size calculation

A pilot study was conducted with ten older adults separated into two groups (*n* = 5) to determine the number of participants we need to recruit. The sample size was calculated considering the primary outcome (functional capacity evaluated using the Glittre-ADL test), a significance level of α = 0.05 and 80% power, resulting in 22 participants to which 20% was added to compensate for possible dropouts. Thus, the sample will be composed of 28 participants, 14 in the intervention group (multicomponent training combined with active tDCS) and 14 in the control group (multicomponent training combined with sham tDCS). The calculation was performed using the G*POWER 3 software and repeated-measures analysis of variance (ANOVA) F test, considering the difference in the time required to complete the test in the pilot study (mean of 172.05 s in group 1 and 203.82 s in group 2, with a standard deviation of 30.79 s).

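### Baseline Glittre-ADL serves as an ANOVA time level and a homogeneity check; adjusting for it as a covariate would give a more precise between-arm comparison, by an amount that depends on an unstated correlation

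*Protocol article*

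**What the plan says.** Under Data analysis, the protocol article compares the arms with "An ANOVA of two factors followed by the Bonferroni test", applied to the active and sham groups over the time points before and after training. Baseline is therefore one level of the outcome. The same section adds that "functional capacity (Glittre-ADL test) will be compared at baseline to ensure homogeneity of the groups". No covariate is named. Missing data are to be handled by intention to treat, "using the appropriate imputation method according to the missing standard".

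The Sample size calculation section sizes the trial on Glittre-ADL with "a significance level of α = 0.05 and 80% power", a "repeated-measures analysis of variance (ANOVA) F test", and pilot values described as a "mean of 172.05 s in group 1 and 203.82 s in group 2, with a standard deviation of 30.79 s". This is reported as "resulting in 22 participants to which 20% was added to compensate for possible dropouts". The total is 28: "14 in the intervention group (multicomponent training combined with active tDCS) and 14 in the control group".

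**The concern.** Two things look wrong.

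First, a baseline comparison does not ensure anything. After proper randomisation any baseline difference is due to chance. A non-significant result in 28 people leaves room for gaps that matter: Assessment of functional capacity counts an improvement of 7 to 40 s as clinically important.

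Second, with baseline as a time level, the group-by-time interaction over two visits is the comparison of mean change scores. That subtracts the full baseline value, whatever its correlation with the later value. A model with baseline as a covariate subtracts only the part that predicts the outcome, so its residual variance is lower. In a small trial this is precision lost from a measurement that is already collected.

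**Working it through.** **Inputs from Sample size calculation.** Difference 203.82 − 172.05 = 31.77 s; SD 30.79 s; d = 31.77/30.79 = 1.032; f = d/2 = 0.516; alpha 0.05; 14 per arm, or 11 per arm (22 evaluable) after the planned dropout.

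**Assumptions, not in the documents.** The baseline-to-post correlation rho is not given, so a range is shown. The rater ICCs near 0.90 in Assessment of functional capacity are reliabilities, not correlations across 12 weeks of training. The section does not say at which visit the SD was taken; it is assumed equal at both visits.

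**The plan's own figure.** For a between-factors repeated-measures F test, lambda = f²·N·m/(1+(m−1)rho). With m = 3 and rho = 0.5 (neither stated), lambda = 0.2662 × 22 × 3/2 = 8.78 on 1 and 20 df. Power is 0.805, so N = 22 reproduces. 22/0.8 = 27.5, rounded up to 28. This is not a calculation for the pre/post group-by-time interaction.

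**The homogeneity check.** SE of the baseline gap = 30.79 × √(2/14) = 11.6 s. Times t(26) = 2.056, this gives 23.9 s. Any smaller gap passes.

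**The two analyses at one follow-up visit.**
- Interaction (change score): variance factor 2(1−rho), df 2n−2.
- Baseline-adjusted: variance factor 1−rho², df 2n−3.
- Ratio: (1−rho²)/[2(1−rho)] = (1+rho)/2.

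Power is from the noncentral t with ncp = 31.77/[30.79 × √(factor) × √(2/n)]. Worked case, n = 14, rho = 0.5:
- Interaction: factor 1, ncp = 31.77/11.64 = 2.73, power 74.8%.
- Adjusted: factor 0.75, SE = 11.64 × 0.866 = 10.08, ncp = 3.15, power 85.8%.

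| rho | variance ratio | 28 evaluable: interaction → adjusted | 22 evaluable: interaction → adjusted |
|---|---|---|---|
| 0.3 | 0.65 | 60.3% → 78.5% | 49.5% → 67.3% |
| 0.5 | 0.75 | 74.8% → 85.8% | 63.4% → 75.5% |
| 0.7 | 0.85 | 92.4% → 95.7% | 84.4% → 89.5% |
| 0.8 | 0.90 | 98.6% → 99.2% | 95.3% → 96.9% |

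**Allowance for chance baseline imbalance.** This inflates the adjusted variance on average by 1 + 1/(2n−4), which is 25/24 at n = 14 and 19/18 at n = 11. Adjusted power becomes 76.9%, 84.3%, 94.9% and 99.0% with 28 evaluable, and 64.9%, 73.2%, 87.8% and 96.1% with 22. The variance advantage then disappears only when (1+rho)/2 exceeds 24/25 or 18/19, that is, rho above 0.92 or 0.895. At rho 0.9 both analyses have power of at least 99.9%.

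**Which ANOVA term.** The interaction is the more favourable reading of the plan. The group main effect averages the outcome with a baseline that treatment cannot have changed, which halves the difference; its power at 14 per arm and rho 0.5 is about 33%.

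**The case against.** The strongest reply is that the planned analysis is valid. In a randomised trial the group-by-time comparison is unbiased, so the point is one of efficiency. That stands. A reader might infer from the 24 s figure that the treatment estimate is biased. It is not: 24 s is the 5% rejection threshold, hence an extreme chance result, and it is a raw baseline gap. Given such a gap, the change-score estimate is displaced by (1−rho) times it (about 12 s at rho 0.5), and over repeated randomisations the displacement averages zero.

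A second reply is that the gain rests on an assumed rho and may be small. That also stands. A reader might take 75% to 86% as the size of the loss; the documents do not support any single figure. Nor do they support saying that adjustment restores 80% power after dropout: with 22 evaluable and rho 0.5 it gives 75.5%.

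A reader might further infer that adjustment is free or removes chance imbalance. It spends a degree of freedom, and it accounts only for the linear effect of baseline Glittre-ADL, not for other characteristics.

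Finally, the unspecified imputation method might look like part of the defect. It is not: an article commonly leaves that detail to the full protocol or analysis plan, and this one does commit to intention to treat.

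What the replies do not answer is that the article itself fixes the model and the purpose of the baseline comparison.

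**Conclusion.** The point holds as one of efficiency and wording. The baseline comparison cannot do what it is said to do, and the stated ANOVA uses baseline less well than a covariate would. The gain in power with 28 evaluable is about 18, 11, 3 and under 1 percentage points at rho 0.3, 0.5, 0.7 and 0.8; with 22 evaluable it is about 18, 12, 5 and under 2 points. The allowance for chance imbalance lowers each slightly. These figures rest on an assumed rho, an SD of 30.79 s at both visits, a true difference of 31.77 s and a single follow-up visit. They do not show that the planned analysis is invalid or that the protocol's figure of 22 is wrong.

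**What to change.** In Data analysis, make the primary between-arm analysis of Glittre-ADL a model with baseline Glittre-ADL as a covariate. Either of these would serve:
- ANCOVA on the post-training time; or
- a mixed model on the post-training and 30-day times with arm, visit, arm-by-visit and baseline, stating which visit carries the primary comparison.

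Report the adjusted arm differences with 95% confidence intervals. Keep the planned intention-to-treat handling, so that randomised participants without follow-up values are not dropped. Report within-arm change from before to after training descriptively, since the Objectives section asks for it. Replace the baseline significance comparison with a descriptive table by arm.

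The cost is a change of wording and one degree of freedom. The data are already collected, the named software (SPSS) fits either model, and nothing changes for participants.

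### Missing outcomes are to be filled in by a method chosen from the missing-data pattern and then tested by a two-factor ANOVA; if the filling is single imputation, the tDCS effect or its error rate can be distorted

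*Protocol article*

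**What the plan says.** In the Protocol article, Data analysis, the rule for dropouts and missing data is that "an intention-to-treat analysis will be performed using the appropriate imputation method according to the missing standard". I read the last words as the missing-data pattern. The rest of that sentence is hard to follow but points to analysis by assigned group. No imputation method is named, and no rule links a pattern to a method.

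The between-group analysis in the same section is a group-by-time ANOVA: "An ANOVA of two factors followed by the Bonferroni test will be used for comparative analysis between groups (active and sham tDCS". It is the only between-group test of the outcomes described, and nothing is said about combining results over several imputed data sets.

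The Sample size calculation section shows how much missing data the design allows for: "resulting in 22 participants to which 20% was added to compensate for possible dropouts". The total is then 28, or 14 per arm.

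**The concern.** Both arms receive the same 12-week training, so both should improve on the Glittre-ADL time whether or not tDCS adds anything. That makes the filling method matter:

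- Last value carried forward gives each dropout no training gain. A real between-arm effect shrinks. If one arm loses more people, the shared training gain appears as a between-arm difference.
- Filling with an arm mean or a regression prediction adds values with too little scatter. An ordinary ANOVA counts them as observed, so its standard error is too small.
- Multiple imputation with pooling avoids both problems, but the text neither requires it nor describes a pooling step.

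With 14 per arm, the handling of about six people can change the conclusion. The clause lets the observed pattern settle the method.

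**Working it through.** **The plan's own figures.** Inputs from Sample size calculation: "mean of 172.05 s in group 1 and 203.82 s in group 2, with a standard deviation of 30.79 s", α = 0.05, power 80%.

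- Difference = 203.82 − 172.05 = 31.77 s; d = 31.77/30.79 = 1.032; f = d/2 = 0.516.
- Repeated-measures ANOVA, between-groups F test, with m = 3 visits and correlation ρ = 0.5 (assumed, not in the article): λ = N f² m/(1 + (m − 1)ρ) = 22 × 0.266 × 3/2 ≈ 8.78. Power is 0.805, so N = 22 is reproduced.
- Dropout: 22/(1 − 0.20) = 27.5, rounded up to 28. The allowance is 28 − 22 = 6 people.

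**Last value carried forward, by arithmetic.** Let g be the training gain (reduction in time) in both arms and δ the extra gain from active tDCS. Dropout is unrelated to outcome.

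- True effect, 3 lost per arm: (g + δ) × 11/14 − g × 11/14 = δ × 11/14 = 31.77 × 11/14 = 25.0 s, whatever g is.
- No effect, 5 versus 1 lost: false difference = g × (5 − 1)/14. For g = 7, 30 and 40 s this is 2.0, 8.6 and 11.4 s.
- True effect, 5 active and 1 sham lost, g = 30: 61.77 × 9/14 − 30 × 13/14 = 39.7 − 27.9 = 11.9 s.

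**Error rates, by simulation.** 14 per arm, SD 30.79 s, pre and post values bivariate normal, t test on change (the group-by-time test with two visits), 20,000 to 40,000 trials per setting. The values of g and ρ are assumptions.

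| Setting | Method | Result |
|---|---|---|
| No effect, 5 vs 1 lost, g = 30, ρ 0.5–0.7 | Last value carried forward | false difference about 8.5 s, type I error 10–12% |
| Same, g = 7, ρ 0.5 | Last value carried forward | 2.0 s, 5.6% |
| Same, g = 20, ρ 0.5 | Last value carried forward | 5.7 s, 7.3% |
| Same, g = 40, ρ 0.5 | Last value carried forward | 11.4 s, 12.9% |
| No effect, 3 vs 3 lost | Arm-mean filling | type I error about 8% |
| No effect | Single regression filling | type I error 9–12% |
| Effect 31.77 s, 3 vs 3, g = 30, ρ 0.5 | Last value carried forward | 25.0 s, power 45% (observed cases about 63%) |

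A second set drew dropout at random at 20% per arm or 30% versus 10%, either completely at random or dependent on baseline, with g = 20 s, ρ 0.5 or 0.7 and 3,000 trials per setting. Arm-mean filling gave type I error of 7 to 9%, and deterministic regression filling 10 to 12%. Multiple imputation (20 imputations, Rubin's rules) gave 4.0 to 4.6%, with estimates of 31.4 to 32.3 s for a truth of 31.77 s.

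**The proposed replacement.** A likelihood-based mixed model on the observed values kept type I error at about 5% and was essentially unbiased. Its power was about 68%, against 62 to 63% for observed cases. Part of that margin depends on the reference distribution used for the test, so power is not the reason to adopt it.

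**The case against.** The strongest reply is that an article need not name an algorithm. It commits to intention-to-treat, to imputation and to a method that suits the missing data, and a separate analysis plan may supply the rest. Multiple imputation fits the wording and behaves well. This stands in part: the text does not commit to a bad method. But it does more than stay silent. It states a pattern-dependent choice and pairs it with an ANOVA that has no pooling step.

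Several stronger readings are tempting and are not supported:

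- *The plan will use last value carried forward or another single imputation.* No method is named.
- *Six dropouts are expected.* The 20% is an allowance, not a forecast.
- *The ANOVA will discard anyone who misses a visit.* The plan proposes imputation, so that analysis is not the one described.
- *The method can be steered towards active tDCS.* Under Allocation and blindness, the analysis table carries only groups 1 and 2, and the labels are not revealed until the 30-day analyses are complete. That limits steering, although it does not fix the method in advance.
- *Carrying values forward inflates false positives in general.* It does so only when dropout is unequal. If six losses fall at random, a split of 5 to 1 or worse has probability 2 × [C(14,5) × 14 + C(14,6)]/C(28,6) = 62,062/376,740, about 16%. Averaged over random splits, there is no bias and type I error is 4.7 to 5.3%.

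The 45% power is also one point. Across the gains and correlations tried, power with last value carried forward and 3 lost per arm ran from 37% to 79%.

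**Conclusion.** The concern holds as a conditional one. The stated route of open imputation followed by ANOVA includes common methods that would give a wrong effect size or a wrong error rate, and nothing in the article rules them out.

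The shrinkage to about 25 s under last value carried forward needs only three losses per arm and a training gain common to both arms. The false difference of about 8.5 s needs both unequal dropout and a gain near 30 s. It lies just inside the 7 to 40 s that the article treats as clinically important (Assessment of functional capacity). The 8 to 12% type I error belongs to arm-mean and single regression filling. The correlation, training gain, dropout split and missingness mechanism are assumptions, since the article gives none of them. The sample size of 28 is not affected.

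**What to change.** Replace the open imputation clause and the two-factor ANOVA with one method fixed before the outcome data are examined. This would be a linear mixed model for Glittre-ADL time with group, visit and group-by-visit, using all observed values of all randomised participants as assigned, with no filled-in values. With 28 people, the test should use small-sample degrees of freedom.

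An acceptable alternative is multiple imputation with the imputation model, the number of imputations and pooled inference all stated in advance.

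The cost is a paragraph of wording and slightly more analysis work, with no change to sample size, visits or treatment. The model assumes that missingness depends only on observed data. An optional sensitivity analysis that gives active-arm dropouts sham-like outcomes after withdrawal would show how far the conclusion rests on that.
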